### 2.6. Blinding and Informed Consent

In this study, the participants will be informed that they have a 50% chance of being allocated in either of the two groups: He's* Santong* needling method plus swallowing rehabilitation training in the treatment group and swallowing rehabilitation training in the control group. Hence participants will not be blinded to their group allocation. Furthermore, it is unfeasible to blind the acupuncturist because of the nature of the intervention; they will be required to minimize communication with participants or outcome assessor regarding treatment procedures and responses. However, outcome assessors and statisticians will be blind to allocation throughout the entire trial.

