### 2.7. Interventions

The acupuncture points were determined according to records in ancient and modern books and results of previous research on acupuncture treatment for dysphagia after stroke [14]. All participants will go through a standardised interview and will be provided with details of the study. The acupuncturist who deliver treatments for treatment group are registered with the Ministry of Health of the People's Republic of China as Chinese medicine practitioners and have more than 20 years clinical experience. Before the trial begins, all acupuncturists will receive special training regarding the purpose and standard procedure of the trial, treatment strategies, and quality control. The treatment details will be fully documented in accordance with the Standard Protocol Items for Randomized Trials (STRICTA) and good clinical practice guidelines [25].

All participants will receive 4-week therapy for five sessions each week. In the treatment group, participants will receive He's* Santong* needling method and swallowing rehabilitation training. In the control group, participants will be treated with swallowing rehabilitation training.

He's* Santong* needling method has three acupuncture procedures:* Weitong* (normal needling),* Wentong* (fire needling), and* Qiangtong* (bloodletting). The* Weitong *procedure will be received five sessions every week, and the* Wentong* and* Qiangtong* procedure will be given two sessions per week on weekdays.

The swallowing rehabilitation training consists of indirect behavioral exercises (e.g., appropriate dietary modification) and direct behavioral exercises (e.g., effortful swallowing and supraglottic swallow technique) according to the Chinese expert consensus for stroke rehabilitation evaluation and treatment, under the direction of rehabilitation practitioners [26]. The 30-minute swallowing rehabilitation session will be carried out by the same rehabilitation practitioner for each participant.

Both groups will receive secondary prevention of ischemic stroke including antiplatelet, antihypertensive, and hypolipidemic therapy according to Chinese Guidelines for Diagnosis and Treatment of Acute Ischemic Stroke [27].

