#### 2.7.1. The Acupuncture Points Used in He's Santong Needling Method

*(1) Weitong (Normal Needling)*. The points in the* Weitong *procedure (needle retention for 30 minutes) are bilateral GB20 (Fengchi), GV16 (Fengfu), TE17 (Yifeng), CV23 (Lianquan), Jialianquan, ST40 (Fenglong), and HT5 (Tongli) (see Figure 2).

All needles will be inserted 10 to 15 mm in depth and manually manipulated with rotation methods to produce a characteristic sensation known as De Qi (feeling of needle sensation that refers to the tenseness around the needle felt by the practitioner and numbness, distension, soreness, and heaviness around the point felt by the participant).

*(2) Wentong (Fire Needling)*. The points in the* Wentong *procedure are bilateral GB20 (Fengchi) and CV23 (Lianquan) (see Figure 2).

The fire needle used in this study is made of manganese and tungsten alloy which will maintain hardness at high temperatures. When the fire needle has been burnt red-hot over a spirited lamp, the acupuncturist will insert the red-hot needle into GB20 and CV23 to a depth of 10mm and then withdraw swiftly without needle retention. The needle hole will be pressed with a sterilized dry cotton-ball [28].

*(3) Qiangtong (Bloodletting)*. The points in the* Qiangtong *procedure are EX-HN12 (Jinjin), EX-HN13 (Yuye), and Yanhoubi (see Figure 2)

Before bloodletting on EX-HN12 and EX-HN13, the acupuncturist will raise the tongue with a spatula and stab the sublingual veins to release 1-2 drops of blood with a three-edged needle after strict disinfection. When performing on the Yanhoubi, the acupuncturist will keep the participant's mouth open with a retainer and press the tongue with a spatula and release 1-2 drops of blood from the pharynx posterior wall with a three-edged needle after strict disinfection [28].

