### 2.8. Outcome Measurement

#### 2.8.1. Primary Outcome

*Penetration-Aspiration Scale (PAS) with Fiberoptic Endoscopic Examination of Swallowing (FEES)*. Participants will receive the Fiberoptic Endoscopic examination of Swallowing (FEES) through the fiberoptic endoscopy. They are requested to swallow stained solid food (1 × 1 × 0.5 cm), semi-liquid food (5 ml), and flow food (5 ml and 10ml) in order. If aspiration occurs, the assessment will be terminated. Aspiration will be defined as the entry of stained food into the airway below the levels of the true vocal cords. Silent aspiration will be defined as aspiration occurring in the absence of cough or gag reflex [29]. PAS is an 8-point scale to quantify penetration and aspiration severity that ranges over four stages of oral intake: level 1 (no laryngeal penetration), levels 2~5 (laryngeal penetration), levels 6~7 (tracheal aspiration), and level 8 (silent aspiration) [30]. The combination of FEES and the PAS has been shown to provide reliable and valid assessments [31]. Two experienced clinician assessors will provide a PAS score independently. If they are in disagreement, the expert assessor will confirm a PAS score via consensus.

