### 3.2. Combined Acupuncture Technique

It has been demonstrated that ordinary acupuncture is an effective and safe treatment for dysphagia after stroke [40]. Compared with ordinary acupuncture, He's* Santong* needling method (*Weitong* (normal needling),* Wentong* (fire needling), and* Qiangtong* (bloodletting)) is a combined acupuncture technique, which is often applied to complications after stroke. For effective aspect, He's* Santong* needling method has the potential to increase therapeutic efficacy for dysphagia after stroke, since it combines three monotherapies. For safety aspect, fire needling and bloodletting have been widely used in China for thousands of years [23]. A set of national standard* standardised manipulations of acupuncture and moxibustion* has been established to ensure the safety of acupuncture techniques including bloodletting and fire needling (GB/T 21709.12-2009 and GB/T 21709.4-2008) [28].

It should be noted that our study has certain methodological limitation. Blinding is a crucial measure to assure the quality of the trial. As a limitation, it is difficult to implement blinding in participants because we will adopt a special acupuncture method. In order to overcome this problem, we will minimize the interaction between the participants and acupuncturists. In addition, all outcome assessors and statisticians will be kept blind throughout the whole process.

To our knowledge, this trial is the first attempt to investigate the efficacy of He's* Santong* needling method on dysphagia after stroke. The results of this trial may develop the clinical treatment of dysphagia. However, the biological mechanism of this therapy requires further investigation.

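### Assessor blinding is claimed without qualification, but the design described does not secure it: one-arm procedures in the examined area, and unblinded participants, could reveal allocation when PAS is rated

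*Protocol article*

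**What the plan says.** Section 2.6 of the protocol article says of participants: "Hence participants will not be blinded to their group allocation". It accepts that acupuncturists cannot be blinded, and requires that "they will be required to minimize communication with participants or outcome assessor regarding treatment procedures and responses". It then gives an unqualified assurance: "However, outcome assessors and statisticians will be blind to allocation throughout the entire trial". Section 3.2 acknowledges that participant blinding is a limitation. Its answer is to limit contact between participants and acupuncturists, and it repeats that "all outcome assessors and statisticians will be kept blind throughout the whole process".

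Section 2.7 gives the control arm no needling and no sham: "In the control group, participants will be treated with swallowing rehabilitation training". In section 2.7.1 the treatment arm's bloodletting includes the sublingual veins, and a step to "release 1-2 drops of blood from the pharynx posterior wall with a three-edged needle". For fire needling the acupuncturist will "insert the red-hot needle into GB20 and CV23 to a depth of 10mm"; the section mentions a needle hole that is pressed afterwards.

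For the primary outcome (section 2.8.1) the participant swallows test foods under fiberoptic endoscopy. "Two experienced clinician assessors will provide a PAS score independently", and an expert assessor settles disagreements. Section 2.8.2 and Table 1 place all efficacy assessments at Week 0 and Week 4.

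**The concern.** Participants and acupuncturists know the allocation, so assessor blinding is the main protection against detection bias. PAS needs that protection because it is a judgement on an eight-level scale. The article's assurance is absolute, yet its own intervention section places one-arm punctures in the region that the primary outcome examines, and its safeguards deal with a different risk, namely what acupuncturists say. If assessors can recognise or learn the arm, a difference in PAS could partly reflect expectation. Later analysis cannot separate that from a treatment effect.

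**Working it through.** **Exposure by arm (section 2.7).** Fire needling: 2 sessions per week × 4 weeks = 8. Bloodletting: 2 × 4 = 8. Normal needling, which also uses CV23: 5 × 4 = 20. Control arm: 0 of each.

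**Procedure sites against assessments (sections 2.7.1, 2.8.1, 2.8.2).**

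- Posterior pharyngeal wall: FEES is an endoscopic examination, and section 3.1 chooses it because the study concerns the oral and pharyngeal phases of swallowing. This is the substantive overlap with the primary outcome.
- Sublingual veins: MMASA includes tongue movement, tongue strength, gag and palate items, so the assessor looks at the mouth. It has no item on the veins themselves. The overlap is partial.
- CV23: an external needle site, relevant only to an assessor who sees the participant in person. The sEMG result is an instrument reading averaged over three recordings, which leaves less room for judgement.
- GB20: no described assessment examines it.

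**Timing.** Treatment runs through Week 4, and the endpoint is at Week 4. No interval after the last procedure is given.

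**Safeguards against routes of unblinding.** There are two routes.

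- Visible marks: no safeguard in section 2.6 or 3.2 addresses them.
- Disclosure by participants: the measures restrict acupuncturists' communication with participants and assessors, and contact between participants and acupuncturists. Neither covers what a participant tells an assessor. Participants know their arm and must score at least 8 on the abbreviated mental test (section 2.4.1). MMASA includes auditory comprehension and expressive dysphasia, so it involves interaction. This route exists even if no mark is ever seen.

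**Illustration of what a rating bias would do.** Section 2.11 gives 30 per group, and 30 × 2 = 60 matches its stated total. Section 2.12 gives two-sided α = 0.05. The bias b, in SD units, is assumed. With no true effect and a normal approximation to a comparison of means:

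SE = √(2/30) = 0.258 SD

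Rejection rate = Φ(b/SE − 1.96) + Φ(−b/SE − 1.96)

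| Assumed b (SD) | b/SE | Rejection rate |
|---|---|---|
| 0 | 0 | 5.0% |
| 0.1 | 0.387 | 6.7% |
| 0.2 | 0.775 | 12.1% |
| 0.3 | 1.162 | 21.3% |
| 0.5 | 1.936 | 49.1% |

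The article gives no SD for PAS. If it were 2 to 2.5 levels (assumed), 0.2 SD would be 0.2 × 2 = 0.4 to 0.2 × 2.5 = 0.5 of a level on average.

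**The case against.** A reader might infer that the procedures leave marks that assessors will see, so that blinding fails. The documents do not support that. They describe one or two drops of blood and a swiftly withdrawn needle whose hole is pressed. They do not say how long any mark lasts, when in Week 4 the assessment falls relative to the last session, or whether PAS is scored live or from recordings. This part of the objection stands.

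It can also be said that operational blinding detail belongs in the full protocol, which is not shown. That is fair as far as silence goes. But the article goes beyond silence: it makes an absolute claim and names its protections, and those protections miss the routes that its own procedures create.

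Two independent raters with an expert arbiter limit individual scoring error. They do not restore blinding if all of them can recognise the arm. PAS is also judged on where stained food goes, not on the state of the pharyngeal wall. That limits what a mark can do to the score, but it does not stop a rater who knows the arm from leaning between adjacent levels.

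Finally, a reader might take the article to be presenting SWAL-QOL as blinded. It does not: participants are openly unblinded, and the claim covers assessors and statisticians. SWAL-QOL needs only a clarifying sentence.

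**Conclusion.** The concern holds in a limited form: assessor blinding is asserted but not secured, and allocation could be revealed at the PAS rating and, less so, at MMASA. The firm elements are the one-arm procedures, the pharyngeal site, their continuation into the endpoint week, and safeguards that leave marks and participant disclosure uncovered. The documents do not establish that blinding will fail, or how large any bias would be. The 12% false-positive rate depends on an assumed bias of 0.2 SD and a normal approximation, and is not a property of this trial. The planned sample size and the choice of tests are unaffected.

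**What to change.** - Record every FEES. Have the two planned assessors, and the expert who settles disagreements, score PAS only from coded clips in random order, with arm and time point hidden, cropped to the laryngeal view where possible, and without contact with the participant.
- Instruct participants not to disclose their group to assessors.
- Have assessors record their guess of allocation at Week 4, and report the result.
- Qualify the statements in sections 2.6 and 3.2: say what assessors see and how they are masked, and note that SWAL-QOL reflects the views of unblinded participants.

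The cost is a little work to export and code recordings; the assessors are already planned. A mark on the pharyngeal wall may still be visible in some clips, so masking would be improved but not guaranteed, which is a reason to report the allocation guesses. The change should be in place before assessments are made, because an examination that was not recorded cannot be re-read masked.

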### 2.7. Interventions

The acupuncture points were determined according to records in ancient and modern books and results of previous research on acupuncture treatment for dysphagia after stroke [14]. All participants will go through a standardised interview and will be provided with details of the study. The acupuncturist who deliver treatments for treatment group are registered with the Ministry of Health of the People's Republic of China as Chinese medicine practitioners and have more than 20 years clinical experience. Before the trial begins, all acupuncturists will receive special training regarding the purpose and standard procedure of the trial, treatment strategies, and quality control. The treatment details will be fully documented in accordance with the Standard Protocol Items for Randomized Trials (STRICTA) and good clinical practice guidelines [25].

All participants will receive 4-week therapy for five sessions each week. In the treatment group, participants will receive He's* Santong* needling method and swallowing rehabilitation training. In the control group, participants will be treated with swallowing rehabilitation training.

He's* Santong* needling method has three acupuncture procedures:* Weitong* (normal needling),* Wentong* (fire needling), and* Qiangtong* (bloodletting). The* Weitong *procedure will be received five sessions every week, and the* Wentong* and* Qiangtong* procedure will be given two sessions per week on weekdays.

The swallowing rehabilitation training consists of indirect behavioral exercises (e.g., appropriate dietary modification) and direct behavioral exercises (e.g., effortful swallowing and supraglottic swallow technique) according to the Chinese expert consensus for stroke rehabilitation evaluation and treatment, under the direction of rehabilitation practitioners [26]. The 30-minute swallowing rehabilitation session will be carried out by the same rehabilitation practitioner for each participant.

Both groups will receive secondary prevention of ischemic stroke including antiplatelet, antihypertensive, and hypolipidemic therapy according to Chinese Guidelines for Diagnosis and Treatment of Acute Ischemic Stroke [27].

#### 2.7.1. The Acupuncture Points Used in He's Santong Needling Method

*(1) Weitong (Normal Needling)*. The points in the* Weitong *procedure (needle retention for 30 minutes) are bilateral GB20 (Fengchi), GV16 (Fengfu), TE17 (Yifeng), CV23 (Lianquan), Jialianquan, ST40 (Fenglong), and HT5 (Tongli) (see Figure 2).

All needles will be inserted 10 to 15 mm in depth and manually manipulated with rotation methods to produce a characteristic sensation known as De Qi (feeling of needle sensation that refers to the tenseness around the needle felt by the practitioner and numbness, distension, soreness, and heaviness around the point felt by the participant).

*(2) Wentong (Fire Needling)*. The points in the* Wentong *procedure are bilateral GB20 (Fengchi) and CV23 (Lianquan) (see Figure 2).

The fire needle used in this study is made of manganese and tungsten alloy which will maintain hardness at high temperatures. When the fire needle has been burnt red-hot over a spirited lamp, the acupuncturist will insert the red-hot needle into GB20 and CV23 to a depth of 10mm and then withdraw swiftly without needle retention. The needle hole will be pressed with a sterilized dry cotton-ball [28].

*(3) Qiangtong (Bloodletting)*. The points in the* Qiangtong *procedure are EX-HN12 (Jinjin), EX-HN13 (Yuye), and Yanhoubi (see Figure 2)

Before bloodletting on EX-HN12 and EX-HN13, the acupuncturist will raise the tongue with a spatula and stab the sublingual veins to release 1-2 drops of blood with a three-edged needle after strict disinfection. When performing on the Yanhoubi, the acupuncturist will keep the participant's mouth open with a retainer and press the tongue with a spatula and release 1-2 drops of blood from the pharynx posterior wall with a three-edged needle after strict disinfection [28].

### 2.8. Outcome Measurement

#### 2.8.1. Primary Outcome

*Penetration-Aspiration Scale (PAS) with Fiberoptic Endoscopic Examination of Swallowing (FEES)*. Participants will receive the Fiberoptic Endoscopic examination of Swallowing (FEES) through the fiberoptic endoscopy. They are requested to swallow stained solid food (1 × 1 × 0.5 cm), semi-liquid food (5 ml), and flow food (5 ml and 10ml) in order. If aspiration occurs, the assessment will be terminated. Aspiration will be defined as the entry of stained food into the airway below the levels of the true vocal cords. Silent aspiration will be defined as aspiration occurring in the absence of cough or gag reflex [29]. PAS is an 8-point scale to quantify penetration and aspiration severity that ranges over four stages of oral intake: level 1 (no laryngeal penetration), levels 2~5 (laryngeal penetration), levels 6~7 (tracheal aspiration), and level 8 (silent aspiration) [30]. The combination of FEES and the PAS has been shown to provide reliable and valid assessments [31]. Two experienced clinician assessors will provide a PAS score independently. If they are in disagreement, the expert assessor will confirm a PAS score via consensus.

#### 2.8.2. Secondary Outcomes

*Saitoh's Classification of Dysphagia*. Saitoh's classification divides the swallowing function into 7 levels: (1) saliva aspirator, (2) food aspirator, (3) water aspirator, (4) chance aspirator, (5) oral problems, (6) minimal problems, and (7) normal. A lower score means more severe swallowing disorder [32].

*Swallowing-Related Quality of Life (SWAL-QOL)*. The scale consists of 44 entries, including appetite, food choice, eating time, symptom frequency, psychological burden, fear, language communication, mental health, fatigue, sleep, and social interaction, summaries all aspects of the quality of life of patients with dysphagia. Each entry has 5 different levels ranging from 1 to 5; a lower score represents more severe dysphagia [33].

*The Modified Mann Assessment of Swallowing Ability (MMASA)*. MMASA is a 100-point scale screening tool for identifying eating and swallowing disorders, which includes 12 items from the Mann Assessment of Swallowing Ability (MASA). The 12 items of the MMASA were alertness, cooperation, respiration, expressive dysphasia, auditory comprehension, dysarthria, saliva, tongue movement, tongue strength, gag, voluntary cough, and palate movements. A lower score means more severe swallowing disorder [34].

*Surface Electromyography (sEMG)*. Activity of submental muscles will be evaluated through sEMG, using a Flexcomp Biomonitoring System. sEMG activity will be detected in the anterior belly of the digastric with a pair of electrodes. Participants will adopt a sitting upright position during the sEMG recording. Two electrodes will be placed on the anterior belly of the digastric muscle parallel to longitudinal axis of the muscle, with the reference electrode placed 3 cm apart from the recording electrode. The peak maximum amplitude will be recorded during 2 ml water swallowing. The recordings will be repeated three times and the mean value will be recorded [35].

Abovementioned outcome measurements will be repeatedly assessed at Week 0 and Week 4. Detailed time points of each outcome assessment are provided in Table 1.

### 2.9. Safety Assessment

All adverse events (AEs) during the treatment will be recorded on AE case report in detail, such as time of appearance, intensity of AEs, and possible causes. The investigators will collect information about AEs and assess whether the AEs are associated with the techniques of acupuncture treatment. Participants will be interviewed about any abnormal reactions or feelings. Participants encountering with mild or moderate AEs will be treated according to their symptoms. Severe AEs will be reported to the Research Ethics Committee, which will provide medical advice to the research team within 48 hours, and the Research Ethics Committee will determine whether a termination of the trial is required.

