## 1. Background

Dysphagia after stroke, manifested as difficulty in swallowing, is a common complication affecting between 37% and 78% of stroke patients [1]. Although the majority of patients achieve recovery from dysphagia spontaneously, dysphagia is still present in 11–50% of stroke sufferers at six months after stroke onset. Persistent dysphagia puts them at risk of pneumonia, malnutrition, dehydration, and even death [2]. It has been confirmed that the existence of dysphagia is associated with poor outcome during the subsequent years [3].

Swallowing is considered one of the most complex neuromuscular activities, which involves 26 pairs of muscles, five cranial nerves, and a complex neural network which coordinates swallowing muscles [4]. Sensory input from the oral cavity, pharynx, and larynx to the central pattern generator (CPG) has been shown to affect swallowing initiation, facilitation, and airway protection [5]. Dysphagia after stroke is thought to be due to damage to the swallowing-related cortex and subcortical structures. The recent researches have demonstrated that increased sensory input can drive long-term beneficial neural changes and reorganize brain plasticity of the swallowing cortex [6].

In order to improve the recovery and shorten the recovery time, various therapeutic options exist for dysphagia after stroke, including exercise-based rehabilitation, drugs, surgical rehabilitation, noninvasive brain stimulation (NBS), and neuromuscular electrical stimulation (NMES) [7]. There is no recommended routine clinical treatment for dysphagia after stroke, although several studies have shown that each approach appears to be promising [2, 7]. Effective alternative therapies are needed to be developed.

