#### 2.4.2. Exclusion Criteria

Patients will be excluded if they have (1) presence of dysphagia before stroke, (2) progressive neurological disorder, (3) serious psychological disorder, (4) a history of pacemaker implantation, (5) unstable cardiopulmonary status, and (6) pregnancy, lactation, or insufficient contraception.

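### Section 2.9 sends adverse events to the ethics committee by severe intensity, so an event serious by outcome but moderate in intensity has no stated route to it

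*Protocol article*

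**What the plan says.** Section 2.9 (Safety Assessment) has every AE during treatment recorded in detail, with examples of what to record: "such as time of appearance, intensity of AEs, and possible causes". Intensity is among them; seriousness is not.

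The section then separates events by grade:

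- Lower grades: "Participants encountering with mild or moderate AEs will be treated according to their symptoms".
- Top grade: "Severe AEs will be reported to the Research Ethics Committee, which will provide medical advice to the research team within 48 hours".

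It closes by giving the committee the decision on ending the trial: "the Research Ethics Committee will determine whether a termination of the trial is required". No other body is named as monitoring safety or deciding on termination.

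**The concern.** Intensity and seriousness answer different questions. Intensity says how strong a sign or symptom is. Seriousness depends on outcome: death, threat to life, hospitalisation or a longer stay, lasting disability. A strong but brief pain can be severe without being serious. A pneumonia of moderate intensity that keeps a patient in hospital is serious without being severe.

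The distinction matters here because the reporting rule controls what the committee is stated to see, and the committee decides on termination. The article's Background says of these patients: "Persistent dysphagia puts them at risk of pneumonia, malnutrition, dehydration, and even death". Sections 2.7 and 2.7.1 add needling and bloodletting in and around the mouth and throat in the treatment group, with secondary prevention that includes antiplatelet therapy in both groups. Events with serious outcomes at less than maximal intensity are therefore plausible. If such events have no written path to the committee, it could be asked to judge continuation on an incomplete set of the events that bear on that judgement.

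**Working it through.** There is no figure to reproduce and no formula applies. The check is a reading of the whole article for *severe*, *serious*, *intensity*, AE handling and termination.

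1. **What *severe* means in Section 2.9.** Intensity is the attribute listed for recording ("such as time of appearance, intensity of AEs, and possible causes"). The next grading words are mild and moderate ("Participants encountering with mild or moderate AEs will be treated according to their symptoms"), and *severe* follows directly. In that order it is the third step of a mild, moderate, severe scale.

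2. **Whether seriousness is defined elsewhere.** The word *serious* occurs once in the article, in the exclusion criteria of Section 2.4.2: "3) serious psychological disorder". There is no serious adverse event category and no outcome-based criterion.

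3. **Whether a second reporting route exists.** None is stated. The schedule in Table 1 has a single row for adverse events and says nothing about who is told of them.

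4. **The printed rule applied to the four possible combinations:**

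| Intensity | Serious by outcome | Not serious by outcome |
|---|---|---|
| Mild or moderate | Symptomatic treatment; no report stated | Symptomatic treatment; no report stated |
| Severe | Reported to the committee | Reported to the committee |

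The rule separates the rows, whereas a termination decision depends mainly on the columns. The upper left cell is the gap: events that bear on termination but have no stated path to the committee.

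5. **What the 48 hours covers.** It is the time allowed for the committee's advice. It does not set a deadline for the team's report and does not fill the gap in step 4.

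**The case against.** The best defence is that *severe* is loose English for *serious*. It is paired with notification of the committee, a rapid response and possible termination, which is the usual handling of serious events. The text is also a journal article, and a full protocol that is not shown may define the term. Both points are fair, and they limit what can be concluded: the printed wording may not reflect the authors' intention. They do not remove the point. The article chose to print the trigger, both branches and the deciding body, so this is a stated rule rather than a detail left out for length, and its graded wording points to intensity.

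Some stronger readings are tempting and are not supported:

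- A reader might infer that moderate but serious events will never reach the committee. Section 2.9 does not say that only severe events are reported, and it does not forbid other reports. It states no route for them, which is a weaker claim.
- A reader might infer that events will be missed altogether. The section requires all AEs to be recorded, with no limit by grade or arm, and participants are interviewed about abnormal reactions. The issue is escalation, not capture.
- A reader might infer that causes are judged only in relation to acupuncture. The assessment against the acupuncture techniques sits alongside a record of possible causes in general.
- A reader might object that no comparison of AE rates between arms is described, or that those judging AEs are not said to be blinded. An analysis plan or full protocol that is not shown may cover these matters, so they are not counted here.

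It is also true that the article gives no grading criteria or event rates. The example of a moderate event that prolongs a stay is an illustration, not a forecast.

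**Conclusion.** The point holds in a limited form. Read as printed, Section 2.9 uses intensity as the trigger for reporting to the ethics committee, and an event that is serious by outcome but moderate in intensity has no stated route to the body that decides on termination. This rests on taking *severe* as the top step of the scale in the same passage, which is the natural reading but not the only possible one. Confidence is moderate for that reason.

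The number of events affected cannot be estimated from the document. Nothing in the sample size, the efficacy analysis or the error rates changes. It is a gap in the safety reporting route that should be corrected because it bears on participant protection and costs little to close. It does not call the trial's validity into question.

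**What to change.** In Section 2.9, and in the full protocol if it carries the same wording, replace severe AEs as the reporting trigger with serious adverse events by the standard seriousness criteria. State that this applies in both arms and whatever the intensity. Keep intensity on the AE form as its own item and add a separate field for seriousness. If the authors already meant *serious*, the same edit makes that explicit.

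One consequence follows from the table above: an event that is severe but not serious would no longer be covered by the sentence. If the committee is meant to go on seeing those events, the text should say so as an addition.

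The cost is one reworded sentence, one form field and perhaps a few more reports to the committee. The change concerns only who is told of which events. It leaves the treatment of participants and the criteria for ending the trial as they are.
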